#### Assignment of interventions

##### Treatment allocation and concealment

All participant data will be collected and managed by an external data management contractor, Strategic Data Pty Ltd (now trading as Logicly). Allocation will be conducted using computer-generated random numbers using an automated data management system after completion of the T1 questionnaire. No stratification will be used.

The researchers, including the statistician responsible for the analysis of outcomes, will be blinded until after the completion of analysis to assess the primary outcome (comparing T1 and T2 data), which will take place after completion of T2. The study psychologist will also be unaware of any participant’s allocation unless they describe the video they have seen in the course of their interaction. If this were to occur, the psychologist would not reveal the participant’s allocation to the researchers.

Because they are aware of the content of the video they watch, it will not be possible to totally blind participants to their allocation. However, they will not be made aware that they could have been allocated to watch either an intervention or control video until T3. In the T3 questionnaire, we will explain the existence of the intervention and control group and ask participants to indicate the group to which they believe they have been assigned. Therefore, we will attempt to maintain the blinding of participants to the degree possible within this study design.

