### Procedure

#### Recruitment

Recruitment will occur online. To ensure participation from a broad cross-section of Australian men, we will use a variety of online recruitment methods. We will use our project partners (e.g. Gotcha4Life, a men’s suicide prevention organisation), and personal and professional networks to recruit participants, as well as public channels. We will send a recruitment flyer via email to researchers providing advice to the project, partners and own networks requesting they in turn share the recruitment information with their networks and via their mailing lists, websites and social media accounts, including Twitter, Instagram, Facebook and LinkedIn. We will post the recruitment information on the University of Melbourne student portal and in student newsletters aimed at departments with significant male enrolments such as Engineering, and Business and Commerce. We will also encourage snowballing (for those who participate to also recruit others).

Participants will be informed via the recruitment materials that the study relates to the attitudes of Australian men to mental health and wellbeing. We have chosen to present this aim of the study as it accurately orients participants to the context of the study without creating unnecessary bias by stating more specifically that we are examining the effects of a video on help-seeking intentions for mental health difficulties.

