### Participant timeline

After registering their interest in participation, participants will attend an online information session. After consenting, participants will immediately be given a link to complete the T1 questionnaire, which will include questions about socio-demographics, suicide risk, help-seeking intentions, intentions to encourage other males to seek help, male depression symptoms, self-reliance, health service use, and social support. Following completion of the T1 questionnaire, participants will be randomly assigned to intervention or control groups by the independent data management contractor. Immediately after randomisation, Strategic Data will email participants a link to their allocated online video (intervention or control); they will also receive a reminder to watch the video at day 3. They will be sent the video link again on day 7, along with the link to the T2 questionnaire. The T2 questionnaire will include questions about help-seeking intentions, intentions to encourage other males to seek help, self-reliance, social support, and feedback on the video. If participants do not view the video within 1 week of receiving the link or do not complete the T1 questionnaire, two reminder emails will be sent 10 and 12 days after T1. The link will expire after 1 week and participants will no longer be able to complete the T2 questionnaire. One month after T2, participants will be emailed the T3 questionnaire, which replicates the T1 questionnaire with the exceptions that it also includes questions about the effects of viewing the allocated video and does not include the DSI-SS. Participants will receive two reminders 3 and 5 days after the initial T3 email is sent. The link will expire after 1 week and participants will no longer be able to complete the T3 questionnaire. All participants who complete the T1 questionnaire will proceed to the T3 questionnaire, regardless of whether they complete the T2 questionnaire or watch their allocated video. See Fig. 1 for the timeline for the trial and Table 1 for the schedule of assessments.

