**Fig. 1 Fig1:**
[figure not shown]
Timeline for the trial. *Note:* DSI-SS, Depression Symptom Inventory—Suicidality Subscale [12]. See Table 1 for further information about T1, T2, and T3 questionnaires and timing

**Table 1 Tab1:** Schedule of assessments

Variable	Measure	Timeline		
		T1	T2	T3
*Screening measure*				
Suicide risk	Depression Symptom Inventory—Suicidality Subscale [12]	X		
*Primary outcome measure*				
Help-seeking intentions	General Help-Seeking Questionnaire—Self [13]	X	X	X
*Secondary outcome measures*				
Intentions to encourage other males to seek help	General Help-Seeking Questionnaire—Other [13]	X	X	X
Self-reliance	Conformity to Masculine Norms Inventory 30—Self-reliance subscale [14]	X	X	X
Male depression symptoms	Male Depression Risk Scale-7 [15]	X		X
Health service use	Health Service Use Questionnaire	X		X
*Other measures*				
Socio-demographics	Information about age, postcode, country of birth, language, marital status, current student, highest education, and employment	X		
Social support question	Information about the number of close friends and close relatives	X	X	X
Feedback on video	Information about video enjoyment, likeability, take-home message, degree of intended sharing with others, and belief about impact		X	
Effects of viewing the video	Information about life changes and time spent with friends			X

*Note.* T1, the T1 questionnaire is completed in the online information session; T2, the T2 questionnaire becomes available 7 days after completion of the T1 questionnaire and the survey expires after 1 week; T3, the T3 questionnaire is made available 4 weeks after the T2 questionnaire is completed or expires. The survey link expires after 1 week

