## Trial status

This RCT has been the Australian New Zealand Clinical Trials Registry (No. 12621001008819) [9]. Recruitment commenced on 16 August 2021 and will end on 2 October 2021. Data collection will continue until the end of November 2021.

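### The two groups are disclosed at each man's own T3, which on the protocol's dates can begin while snowball recruitment is open and later T2 answers are outstanding: a small, cheaply avoided unmasking route

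*Protocol article*

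**What the plan says.** The section on treatment allocation and concealment accepts that participants cannot be fully blinded, since each man knows what he watched. What it protects is knowledge of a second condition: "they will not be made aware that they could have been allocated to watch either an intervention or control video until T3". At that point the masking ends by design: "In the T3 questionnaire, we will explain the existence of the intervention and control group and ask participants to indicate the group" they believe they were in.

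The note to Table 1 sets the timing man by man. For T2: "T2, the T2 questionnaire becomes available 7 days after completion of the T1 questionnaire and the survey expires after 1 week". For T3: "the T3 questionnaire is made available 4 weeks after the T2 questionnaire is completed or expires". The participant timeline words the gap slightly differently: "One month after T2, participants will be emailed the T3 questionnaire".

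The calendar is under Trial status: "Recruitment commenced on 16 August 2021 and will end on 2 October 2021". The Recruitment section adds a direct link between earlier and later entrants: "We will also encourage snowballing (for those who participate to also recruit others". That section also explains that the recruitment material deliberately leaves out the focus on a video and on help-seeking, in order to avoid bias.

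The primary-outcome analysis section places the T1 to T2 analysis after all T2 data are in but before T3 data have been collected.

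**The concern.** The masking rule is written for one man at a time, but the trial enrols over almost seven weeks, and a man reaches T3 five weeks or more after entry. The first men are therefore debriefed while others are still joining or still owe a T2 answer. Because participants are asked to bring in others, some of those later men may be in touch with a debriefed one.

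The primary outcome is a self-reported intention and the target difference is small, 0.25 SD. A man who learns before T2 that there is an intervention and a control group may guess what is being tested and answer accordingly. The Discussion relies on comparing change between arms to remove social desirability bias that is the same in both groups. Knowledge of the arms need not act equally on both, so that comparison would not necessarily remove it. The same T2 data also decide whether the video is released.

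**Working it through.** The protocol gives no figure for this overlap, so there is none to reproduce. The check is calendar arithmetic.

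**Inputs from the protocol.** Recruitment runs from 16 August to 2 October 2021, 47 days (Trial status). T2 is answered on day 7 to day 14 after own T1, and T3 opens 4 weeks after own T2 is completed or expires (note to Table 1). The participant timeline says one month, taken here as 31 days. Sample size is 446.

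**Assumptions of mine.** The first T1 is on 16 August and accrual is even.

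**Dates.**
- Earliest T3: 16 August + 7 + 28 days = 20 September.
- Recruitment closes on 2 October, 12 days later.
- Last T2 window closes: 2 October + 7 + 7 days = 16 October, 26 days after the earliest T3.
- Last T3 window closes: 2 October + 14 + 28 + 7 days = 20 November, which fits data collection ending in late November.

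**Share of T2 answers after the first possible disclosure.** Let the first entrant answer T2 on day a, let T3 follow g days later, and let later men answer T2 on day b after their own T1. A man entering after day c = a + g − b answers T2 after the first disclosure. The share is (47 − c)/47.

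| a | g | b | c | share |
|---|---|---|---|---|
| 7 | 28 | 7 | 28 | 19/47 = 40% |
| 7 | 28 | 14 | 21 | 26/47 = 55% |
| 7 | 31 | 7 | 31 | 16/47 = 34% |
| 7 | 31 | 14 | 24 | 23/47 = 49% |
| 14 | 28 | 7 | 35 | 12/47 = 26% |
| 14 | 28 | 14 | 28 | 19/47 = 40% |
| 14 | 31 | 7 | 38 | 9/47 = 19% |
| 14 | 31 | 14 | 31 | 16/47 = 34% |

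The range is about 20% to 55%. With a = 7 and g = 28, a first T1 one week after recruitment opens gives 12/40 = 30% to 19/40 = 48%. Two weeks after, it gives 5/33 = 15% to 12/33 = 36%.

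**Share exposed through a referrer.** Being late is not enough: the referrer must have reached his own T3 before his friend answers T2. With T3 on day 35, he must have entered at least k = 35 − b days before the friend. If the referrer is equally likely to be any earlier entrant, a friend entering on day t meets this with probability (t − k)/t for t > k. Averaged over 47 days:

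share = [(47 − k) − k ln(47/k)]/47

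- b = 7, k = 28: [19 − 28 × 0.518]/47 = 4.50/47 = 9.6%.
- b = 14, k = 21: [26 − 21 × 0.806]/47 = 9.08/47 = 19.3%.

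If 10% to 30% of entrants come by snowballing (assumption), the exposed share is 1.0% to 2.9% in the first case and 1.9% to 5.8% in the second. That is about 1% to 6%, or roughly 4 to 26 of 446 men.

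**Possible bias, for illustration.** If each exposed man's score shifts by 0.5 SD (assumption), an arm mean moves by 0.01 × 0.5 = 0.005 SD, 0.03 × 0.5 = 0.015 SD or 0.06 × 0.5 = 0.03 SD. Opposite shifts in the two arms would double these. The design effect is 0.25 SD.

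**Consistency with the analysis timing.** Some T3 answers can arrive from 20 September and some T2 answers until 16 October. An analysis cannot then follow all T2 data and precede all T3 data. It can precede the completion of T3 collection, but that reading leaves the overlap in place.

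**The case against.** The strongest reply is that the risk is small and largely conceded. The protocol says blinding is kept only as far as the design allows. The exposed share of 1% to 6% assumes that every referrer answers T3 as soon as it opens and always tells his friend before the friend's T2. Men who refer friends soon after their own orientation would have friends who finish T2 well before the referrer's T3. All of this stands, and it is why the point is minor. In the other direction, the figure covers referral only, and contact through shared student or partner networks is not counted.

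A reader might infer from the calendar that masking fails for some 40% of primary outcomes. The documents do not support that: 40% is the share of T2 answers falling after the first possible disclosure under one set of timings, and most of those men need not know anyone who has been debriefed.

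A reader might also infer that a debriefed man can describe both videos. The protocol promises only a brief explanation of the two conditions. Nothing says that the other video's content is given, and he has seen one video.

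Finally, friends in different arms may talk about the intervention video as soon as one has watched it, about a month before T3. That contamination comes from individual randomisation combined with snowballing. It is a separate matter and is not caused by the T3 disclosure.

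The statement on analysis timing could be offered as a safeguard. Read literally it would exclude the overlap, but the individual T3 schedule and the recruitment dates do not allow it to be met.

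**Conclusion.** The overlap follows from the protocol's own schedule. Disclosure can begin on 20 September 2021 with recruitment open for 12 more days and T2 answers possible for up to 26 more, and nothing in the document holds it back. Roughly 20% to 55% of T2 answers fall after the first possible disclosure, given even accrual and a first T1 on the opening day; a later first session lowers this. The share exposed through a referrer is about 1% to 6%, resting on assumed snowballing of 10% to 30% and on referrers drawn evenly from earlier entrants. The expected bias is small against 0.25 SD and does not threaten the trial. It is still an avoidable unmasking route for a self-reported primary outcome, and removing it is cheap. The sentence on analysis timing needs reconciling with the T3 schedule and recruitment dates. Severity: minor.

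**What to change.** Take the explanation of the two groups and the arm-guess item out of the T3 questionnaire. Send them as a short separate debrief once the last T2 window has closed (about 16 October) and, for each man, not before his own T3 is completed or has expired. Reword the analysis-timing statement so that it agrees with individually timed T3 questionnaires, for example by saying that the analysis precedes completion of T3 collection.

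Optionally, record at registration whether a current participant referred the man, and run a sensitivity analysis without referred men. As recruitment has begun, the field would miss men already enrolled, and the analysis would describe a selected subset.

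The cost is one extra automated email, some non-response to the arm-guess item, and a later blinding check: up to about 26 days later for the earliest men. Sample size and arms are unchanged. The change does not remove contamination between friends who discuss the video itself.

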##### Intervention

The intervention is a music video of approximately 4-min length created specifically for this study. It features a large group of diverse men singing a song in a community town hall. The song’s lyrics relate to the need for men to talk to others when experiencing mental health difficulties and to encourage others to do the same. The ‘call to action’ at the end of the video is ‘When the going gets tough. Get Talking’, and then there is a link to a website, which will provide links to further mental health support. This website will not be live during the trial to ensure that we can isolate any effects of the video from any effects of additional actions that might take place after participants watch the video.

##### Control

The control video is a 4-min section of a longer documentary video that relates to improving cognitive processing speed by playing table tennis. We chose this video as it is unlikely to influence the outcomes of interest in the study, and as it relates to brain health, though not mental health, and the study questionnaires will seem relevant to the video. The control video also shares some common features with the intervention video, including that it is the same length, is also Australian, and features only men.

There will be no special criteria for discontinuing or modifying allocated interventions.

#### Treatment adherence

On day 3 after T1, participants will be encouraged via an email reminder including a personalised video link to watch the video. These links will provide participants with unlimited access to their allocated video until the completion of the T2 questionnaire. Participants will be sent the video link again with the link to complete the T2 questionnaire at day 7 after T1. To assess adherence to the intervention, we will record participants’ viewing behaviour related to the intervention and control videos by counting how many times the given video was started, how many times it was watched from beginning to end, when the video was paused, the number of times the participant tried to navigate away from the video page (e.g. by closing the tab or browser) and at what time points in the video the participant left the video page (e.g. 14 s). We will also ask one ‘attention’ question related to the content of the intervention or control video at T2. This is a question the participant can only answer by having attentively watched the video.

#### Relevant concomitant care permitted or prohibited during the trial

Participation in the trial does not require any alteration to participants’ usual care pathways (including use of any medication) in either arm.

#### Provisions for post-trial care

All participants will have free access to short phone consultations with the study psychologist throughout the trial and for 4 weeks following their completion of the trial. The psychologist will refer them to further supports as necessary.

### Participant timeline

After registering their interest in participation, participants will attend an online information session. After consenting, participants will immediately be given a link to complete the T1 questionnaire, which will include questions about socio-demographics, suicide risk, help-seeking intentions, intentions to encourage other males to seek help, male depression symptoms, self-reliance, health service use, and social support. Following completion of the T1 questionnaire, participants will be randomly assigned to intervention or control groups by the independent data management contractor. Immediately after randomisation, Strategic Data will email participants a link to their allocated online video (intervention or control); they will also receive a reminder to watch the video at day 3. They will be sent the video link again on day 7, along with the link to the T2 questionnaire. The T2 questionnaire will include questions about help-seeking intentions, intentions to encourage other males to seek help, self-reliance, social support, and feedback on the video. If participants do not view the video within 1 week of receiving the link or do not complete the T1 questionnaire, two reminder emails will be sent 10 and 12 days after T1. The link will expire after 1 week and participants will no longer be able to complete the T2 questionnaire. One month after T2, participants will be emailed the T3 questionnaire, which replicates the T1 questionnaire with the exceptions that it also includes questions about the effects of viewing the allocated video and does not include the DSI-SS. Participants will receive two reminders 3 and 5 days after the initial T3 email is sent. The link will expire after 1 week and participants will no longer be able to complete the T3 questionnaire. All participants who complete the T1 questionnaire will proceed to the T3 questionnaire, regardless of whether they complete the T2 questionnaire or watch their allocated video. See Fig. 1 for the timeline for the trial and Table 1 for the schedule of assessments.

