### Participant selection

When participants register their initial interest in participating in the RCT via a registration website, they will be sent a detailed Plain Language Statement (PLS) outlining the requirements of trial participation. They must then attend an online orientation session run by one of our researchers and a study psychologist. In these sessions, the researcher will reiterate key background information from the PLS and answer questions to allow participants to provide informed consent. Once participants have had their questions answered, they will complete an online consent form, ticking a box to provide consent to continue to the T1 questionnaire (note that this includes consent to use of de-identified data for additional studies with ethical approval). If they do not consent, they will not proceed to the T1 questionnaire. The Depression Symptom Inventory—Suicidality Subscale (DSI-SS) [12] suicide risk screening questionnaire will be included in the T1 questionnaire. The study psychologist who attends the session will phone any participant who scores 2 or above on the DSI-SS to further assess their risk and to assist the participant in seeking further mental health support if the participant would like it. If the psychologist determines that the participant is at imminent risk of suicide or could be harmed by further participation, they will be excluded from further participation and referred for mental health support. If the participant is not determined to be at risk of harm, they will continue in the trial, but may still be referred for further support as required. The study psychologist will conduct a risk assessment using criteria such as whether the person has a current plan for suicide, and whether they have a history of suicide attempt. Participants will also be supplied with the psychologist’s contact details and able to contact them directly for further support for up to 4 weeks following completion of the T3 questionnaire. Following completion of the T1 questionnaire, participants will be randomised to view the intervention or control video.

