#### Exclusion criteria

Scored ≥ 2 on the DSI-SS [12], and the study psychologist determines that the participant is actively suicidal or likely to experience harm from further participation.

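### Randomisation and release of the video link are tied only to completing T1; nothing visible makes them wait for the psychologist's decision on which the sole exclusion criterion depends

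*Protocol article*

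**What the plan says.** **Screening and exclusion.** Under Participant selection, the DSI-SS "suicide risk screening questionnaire will be included in the T1 questionnaire". The study psychologist "will phone any participant who scores 2 or above on the DSI-SS to further assess their risk". A man judged to be at imminent risk, or liable to be harmed by taking part: "they will be excluded from further participation and referred for mental health support". Otherwise: "If the participant is not determined to be at risk of harm, they will continue in the trial". The Exclusion criteria section lists one criterion, a score of 2 or more, "and the study psychologist determines that the participant is actively suicidal or likely to experience harm from further participation". No time limit is given for the call.

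**Allocation and exposure.** Under Treatment allocation and concealment: "Allocation will be conducted using computer-generated random numbers using an automated data management system after completion of the T1 questionnaire". Participant timeline also places random assignment after T1, and continues: "Immediately after randomisation, Strategic Data will email participants a link to their allocated online video (intervention or control".

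**Follow-up and analysis.** Participant timeline states: "All participants who complete the T1 questionnaire will proceed to the T3 questionnaire", whether or not they complete T2 or watch the video. Statistical analyses defines the intent-to-treat set as everyone randomised.

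**The concern.** Eligibility cannot be known at the moment T1 is completed, because it depends on a conversation that a T1 score sets off. Yet completion of T1 is the only condition the protocol attaches to allocation, and the link follows allocation at once. Two things are at stake.

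- **The screen may act too late.** The DSI-SS is given only at T1 (Table 1). The section on adverse events says that the video refers indirectly to suicide and names distress from viewing as the likeliest harm. A screen meant to catch men who could be harmed by continuing should not be able to finish after they have received the video.
- **The randomised set may contain men who do not meet the entry criteria.** Anyone excluded after allocation stays in the intent-to-treat set with T1 data and no T2 value. The protocol does not say how such a man is handled, and the T3 sentence makes no exception for him.

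**Working it through.** The question is one of sequence, so the main check sets the sections side by side.

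| Step | What it is conditional on | Section |
|---|---|---|
| DSI-SS score | completing T1 | Participant selection; Table 1 |
| Psychologist's call | score of 2 or above; no deadline | Participant selection |
| Exclusion | psychologist's determination | Exclusion criteria |
| Randomisation | completing T1 | Abstract (Methods); Participant selection; Treatment allocation and concealment; Participant timeline |
| Video link | randomisation, at once | Participant timeline |
| T3 questionnaire | completing T1 | Participant timeline |
| Analysis set | being randomised | Statistical analyses |

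1. Four places tie randomisation to completion of T1. None mentions clearance by the psychologist.
2. The contact schedule points to allocation close to T1. The abstract gives access to the video for 1 week after randomisation and sends the T2 link 7 days after T1. Treatment adherence counts the day-3 and day-7 contacts from T1. These clocks agree only if randomisation falls at or near completion of T1. No provision is made for a flagged man whose allocation is delayed.
3. Every man excluded on the psychologist's judgement has completed T1. Taken literally, the T3 sentence includes him and the exclusion rule removes him.

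**Effect on power (illustration only).** The inputs from Sample size and power analysis are a difference of 0.25 SD, 90% power, two-sided 5%, correlation 0.67, 20% loss and N = 446.

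- The plan's figure first: 2 × ((1.960 + 1.282)/0.25)² = 336.24 per arm. Multiplying by the baseline-adjusted factor 1 − 0.67² = 0.5511 gives 185.3. Multiplying by 1.2 gives 222.4, rounded up to 223 per arm, or 446. The stated total is reproduced.
- Assume that a share e of the 446 is excluded after randomisation, on top of the 20% loss. Evaluable men per arm are n = 223 × (1 − e) × 0.8. Power is Φ(0.25 / √(2v/n) − 1.960), where v = 0.5511 (baseline-adjusted) or v = 2(1 − 0.67) = 0.66 (change score).

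| e (assumed) | Men excluded (446 × e) | n per arm | Power, v = 0.5511 | Power, v = 0.66 |
|---|---|---|---|---|
| 0% | 0 | 178.4 | 88.9% | 82.8% |
| 1% | 4.5 | 176.6 | 88.6% | 82.4% |
| 2% | 8.9 | 174.8 | 88.3% | 82.0% |
| 5% | 22.3 | 169.5 | 87.3% | 80.9% |
| 10% | 44.6 | 160.6 | 85.5% | 78.7% |

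At 3%, 446 × 0.03 = 13.4 men would be excluded. For comparison, the loss allowance is 446 × 0.2 = 89 men. What matters here is the change down each column, which is small for small e under either variance.

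**The case against.** The strongest reply is that the order is unstated, not wrong. Participant selection describes the call, the exclusion and continuation before its closing sentence on randomisation. The DSI-SS is labelled a screening measure. The psychologist attends the session in which T1 is completed, so a prompt call is feasible. The word automated describes how allocation is generated, and the immediacy applies to the step from randomisation to the email, not the step from T1 to randomisation. Fig. 1, whose note defines the DSI-SS, may show the order but is not reproduced in the text at hand. An article may also leave the contractor's system settings to the full protocol.

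Much of this stands, and it rules out several stronger readings:

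- **That ineligible men are randomised by design, or that the screen cannot act before exposure.** No section says that the call follows randomisation. The text supports only that this can happen.
- **That exclusion would depend on arm.** The protocol concedes that the psychologist may learn an allocation if a man describes his video, but does not link this to the eligibility call. The bias would need a late call, a video already watched, its content disclosed and a judgement altered by it. None of these is documented.
- **That the T3 sentence is a plain contradiction.** Its remainder shows that it is mainly about following up men who miss T2 or do not watch. The conflict lies in its literal scope.
- **That the trial loses appreciable power.** It does not at small exclusion rates, and the mixed model retains men who have only T1 data.

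The reply does not remove the core. The article does state a sequence, several times, and each time without the eligibility decision. Its contact clocks fit allocation at T1 better than allocation after a call of unspecified timing.

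**Conclusion.** The concern holds in a limited form. As written, allocation and release of the video depend only on completing T1, while eligibility depends on a later decision that no visible passage places before them. A man later found ineligible can therefore be randomised, sent the video and kept in the analysis set without T2 data. The T3 sentence needs narrowing for the same reason.

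The number of men affected is unknown. The figure of 4 to 13 rests on an assumed exclusion rate of 1% to 3%, and the matching loss of power is well under one percentage point at 2%. The case for acting rests on having the screen finish before exposure and on a randomised set that contains only eligible men. It would fall away if Fig. 1 or the full protocol shows that allocation already waits for the decision; the text would then need only to say so.

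**What to change.** Reconcile Participant selection, Exclusion criteria, Treatment allocation and concealment, and Participant timeline so that they give one order:

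1. For anyone flagged by the DSI-SS, the data system holds both allocation and the video link until the psychologist's eligibility decision is recorded. All others are allocated after T1 as now.
2. For flagged men who are cleared, the day-3 and day-7 contacts are counted from randomisation.
3. The T3 sentence refers to all randomised participants instead of all who complete T1.
4. If any man has already been excluded after allocation, state how he is handled in the intent-to-treat analysis.

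The cost is a conditional flag in an existing system and a short delay in allocation for flagged men only. Their interval from T1 to T2 becomes slightly longer, but the hold comes before allocation and so cannot differ by arm. The calls are already planned. The DSI-SS threshold and the psychologist's criteria are untouched.
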